**Investigators:**

Investigators are to wear cloth or surgical mask at all times. Staff to wipe down equipment between each subject use using recommended disinfectant wipes. No food or drink in patient care areas. Staff will carry individual sanitizers for individual or subject use.

**Infection Prevention:**

Equipment wiped off between each subject's use with Super Sani-Cloth germicidal disposable wipes. Polar heart rate monitors and straps will be immediately wiped down with Super Sani-Cloths, and then all straps

will be washed per manufacturers recommendations. Reusable cuffs wiped between classes. Stethoscope disinfected with alcohol between patient. Pulse oximeters wiped with alcohol between each subject use. No equipment with fans to be used; includes Air Dyne bike and rower. No locker use, Restrooms limited to no more than 2 individuals at a time and signage added to restroom doors to notify of 2 person limit, with and washing instruction applied to mirrors. Exercise equipment spaced 6 feet apart.

## Statistical Analysis

Non-inferiority design:  $H_0: \mu_{\text{Mask}} - \mu_{\text{NoMask}} \leq -\delta$  vs.  $H_1: \mu_{\text{Mask}} - \mu_{\text{NoMask}} > -\delta$  where  $\delta > 0$  denote the non-inferiority margin of 3.5, which is a (clinically meaningful) minimal detectable difference. The sample sizes are: Total sample size  $n = 20$   $n_{\text{NoMask}} = (1 + 1/k) * \sigma^2 * ((Z_{1-\alpha} + Z_{1-\beta}) / (d + \delta))^2$   $n_{\text{Mask}} = k * n_{\text{NoMask}}$  where  $\sigma^2$  is the variance, and  $d = \mu_{\text{Mask}} - \mu_{\text{NoMask}}$  is known as the allowable difference, which is the true mean difference between the new treatment (Mask) and the control (NoMask). 1)  $\delta = 3.5 \text{ mlO}_2 * \text{kg}^{-1} * \text{min}^{-1}$  (1 eMET=3.5  $\text{mlO}_2 * \text{kg}^{-1} * \text{min}^{-1}$ ): a (clinically meaningful) minimal detectable difference 2)  $k=1$  : the ratio of the sample size of treatment(mask) group to the sample size of control(NoMask) group 3)  $\sigma^2 = 3.5$ : population eMET change variance 4) power: 0.9 5) 5% expected rate of drop-outs 6)  $d=0$ : Descriptive statistics will be used to characterize the patient cohort. Demographic variables will be described using mean with standard deviations for continuous variables and counts with percentages for categorical variables. The Wilcoxon signed-rank signed test or paired-sample t-test will be used to compare continuous variables between the Mask and NoMask exercise. McNemar's test will be applied to compare categorical variables. Mixed-effected linear regression models will be applied for the repeated measures data. Pearson correlation coefficient will be calculated whenever it is appropriate. Analyses will be two-tailed and performed at significance level of 0.05 with SAS 9.3 software (SAS Institute, Cary, NC).

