## Hypothesis

**Our null hypothesis  $H_0$**  states that exercising with a cloth mask will be inferior to the current standard of exercising without a facemask, limiting peak exercise when non-inferiority margin is 1 estimated metabolic equivalent ( eMET  $3.5 \text{ mlO}_2 \cdot \text{kg}^{-1} \cdot \text{min}^{-1}$ ).

**Our alternative hypothesis  $H_1$**  states that exercising with a mask will not be inferior to the current standard of exercising without a facemask, limiting peak exercise when non-inferiority margin is 1 eMET.

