## EXPERIMENTAL DESIGN & METHODS

**Subject Recruitment:** We will recruit 20 subjects through the Cleveland Clinic. Inclusion Criteria: Healthy subjects age  $\geq 18$ , Exclusion Criteria: Any long-term disease that would interfere with their ability to exercise safely, fever  $\geq 100.4$  F, or pregnancy. Informed consent will be obtained by the CoPI, and need for medical clearance determined based on ACSM's 2015 preparticipation guidelines. (See appendix 12.6) To remain compliant with enterprise guidelines we will not be recruiting healthy subjects outside of the Cleveland Clinic staff at this time to avoid increase COVID-19 exposure risk. However, if the enterprise changes the guidelines we will expand our enrollment to include non Cleveland Clinic employees. Employees will not be solicited by

direct initiation. Recruitment will involve only posted notice or general advertising that does not pressure employees into participating for fear of job loss, delayed promotion, or other influences from their superior.

**Study Design:** The study design is a prospective crossover non-inferiority trial where subjects will complete 3 separate graded exercise treadmill tests each time wearing either No Mask, N-95 Mask (3M), or Cloth Mask (Boco). The order of the mask worn will be randomly assign to minimize familiarization or training effect. All testing will be performed in a Cleveland Clinic facility following standardized COVID-19 screening precautions. We will compare the data collected from each test to asses for differences between subject comfort, peak exercise capacity (eMET), heart rate response during exercise and recovery.

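### The planned 20 subjects for 90% power do not follow from the printed formula and inputs, and the formula is worded for two separate groups although the trial is a crossover

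*Protocol*

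**What the plan says.** The protocol, under Experimental Design & Methods, sets the size: "We will recruit 20 subjects through the Cleveland Clinic". It describes the design there: "The study design is a prospective crossover non-inferiority trial where subjects will complete 3 separate graded exercise treadmill tests". Each subject therefore supplies a result under every condition.

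The Statistical Analysis section prints a sample-size formula containing the factor (1 + 1/k), a variance, a one-sided normal quantile for alpha and a quantile for power. It defines k as "the ratio of the sample size of treatment(mask) group to the sample size of control(NoMask) group" and sets it to 1. The margin is given in mL O2/kg/min: delta is said to "denote the non-inferiority margin of 3.5, which is a (clinically meaningful) minimal detectable difference". The Hypothesis section states the same margin in the other unit: "non-inferiority margin is 1 estimated metabolic equivalent". The variance is 3.5 with no unit, and its label runs on into the next inputs: "population eMET change variance 4) power: 0.9 5) 5% expected rate of drop-outs". The true difference d is 0.

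The numbered inputs contain no alpha. Later in the same section the analyses are two-tailed at 0.05, and the Mask and NoMask results are to be compared with a paired t-test or signed-rank test.

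**The concern.** The protocol fixes the formula, the inputs and the result, so the result can be checked, and it does not come out. Three features of the paragraph explain why a reader cannot repair it unaided.

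- **Design.** The factor (1 + 1/k) and the ratio of group sizes belong to two independent samples. In a crossover the relevant quantity is the variance of the within-subject difference. If the 3.5 is already that variance, the factor doubles the sample size without reason.
- **Meaning and unit of 3.5.** It is printed as a variance of change and labelled eMET, while the margin is in mL/kg/min. SD or variance, per test or difference, and the unit all change the answer greatly.
- **Alpha.** The formula is one-sided, the analysis is two-tailed at 0.05, and the level used for planning is not given.

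This paragraph is the only justification for the number of subjects and the only statement of power. In a non-inferiority trial a failure to exclude the margin is hard to interpret unless the power statement can be relied on.

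**Working it through.** **Inputs (Protocol, Statistical Analysis).** Variance 3.5; delta 3.5 mL/kg/min (1 eMET); k = 1; d = 0; power 0.9; drop-out 5%; total n = 20. Alpha is not listed, so one-sided 0.05 and 0.025 are both shown. Quantiles: 1.645 (0.05), 1.960 (0.025), 1.282 (power 0.9).

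**Step 1: the plan's own calculation.** n per condition = (1 + 1/k) × variance × ((Z for alpha + Z for power)/(d + delta))².

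- One-sided 0.05: 2 × 3.5 × ((1.645 + 1.282)/3.5)² = 7 × 0.699 = 4.89, so 5.
- One-sided 0.025: 2 × 3.5 × ((1.960 + 1.282)/3.5)² = 7 × 0.858 = 6.004, so 7.

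With 5% drop-out: 5/0.95 = 5.3, so 6; and 7/0.95 = 7.4, so 8. In a crossover the number per condition is the number of subjects. Even if the two conditions are added as separate groups, the totals are 10 and 14, or 11 and 15 after drop-out (10/0.95 = 10.5; 14/0.95 = 14.7). The stated 20 is not reproduced.

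**Step 2: a paired calculation.** n = SDd² × ((Z for alpha + Z for power)/(d + delta))², where SDd is the SD of the within-subject difference. The subjects needed and the power below are from the exact paired t-test (noncentral t, n − 1 degrees of freedom). Evaluable pairs: 20 × 0.95 = 19. In each cell, one-sided 0.05 comes first and 0.025 second.

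| Reading of 3.5 | SDd | Margin | Pairs needed for 0.9 | Power at 19 pairs |
|---|---|---|---|---|
| A. Variance of change, (mL/kg/min)² | √3.5 = 1.87 | 3.5 | 5 / 6 | >0.999 / >0.999 |
| B. SD of change, mL/kg/min | 3.5 | 3.5 | 11 / 13 | 0.995 / 0.984 |
| C. Per-test SD, mL/kg/min, variance of difference 2 × 3.5² = 24.5 | 4.95 | 3.5 | 19 / 24 | 0.91 / 0.83 |
| D. Variance of change, eMET² | 1.87 eMET | 1 eMET | 32 / 39 | 0.72 / 0.60 |

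**Step 3: where 20 may come from.** Reading C at one-sided 0.05 needs 19 pairs, and 19/0.95 = 20.0. The printed formula with 3.5 as an SD is close to this: 2 × 3.5² × 0.699 = 17.13, so 18, and 18/0.95 = 18.9, so 19. The exact t version accounts for the remaining subject. The match needs three things the text does not say: that 3.5 is an SD, that it refers to a single test, and that the variance of the difference is twice its square (for example, no correlation between a subject's tests).

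**The case against.** The best defence is reading C. It returns 20 subjects, 90% power and 5% drop-out together, so the likely fault is a mislabelled input and not an unsuitable sample size. The factor of 2 is then legitimate: if 3.5 is a per-test or within-subject error SD, the variance of a difference is twice its square. The number per condition is also rightly taken as the total, because the same people supply both conditions. All of this stands, and it rules out saying that no interpretation gives 20. It does not rescue the text, which prints a variance and calls it a variance of change. Reading C also holds only at one-sided 0.05; at the one-sided level that matches a two-tailed 0.05 test, power is 0.83.

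A reader might infer from the eMET label that units were mixed and that true power is 0.60 to 0.72 (reading D). The protocol does not support that inference. The same word names the endpoint, the conversion to 3.5 mL/kg/min is printed with the margin, and nothing states that the variance is in eMET². Reading D implies an SD of change of 1.87 × 3.5 = 6.5 mL/kg/min, which the protocol nowhere gives.

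It is also fair that the one-sided quantile suits the one-sided alternative hypothesis. What is missing is the alpha used with it and its relation to the two-tailed analysis.

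**Conclusion.** The point holds as a defect in the sample-size statement. With the printed formula and inputs the result is 5 or 7 per condition before drop-out, not 20, and the two-group wording does not match the crossover or the planned paired tests. Taken literally, with 3.5 as a variance of change in the squared unit of the margin, 19 evaluable pairs give power above 0.999, so 0.9 is not the power those inputs imply.

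The size and direction of the error cannot be fixed from the protocol. Power at 19 pairs runs from above 0.999 (A), through 0.91 or 0.83 (C), to 0.72 or 0.60 (D). It would be wrong to conclude that the trial is underpowered: that needs reading D, or reading C with one-sided 0.025, and the protocol establishes neither. All figures assume a true difference of 0, approximately normal differences, a single mask-versus-no-mask comparison and 5% loss.

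**What to change.** Keep 20 subjects and replace the sample-size paragraph. It should:

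1. use the paired formula, n = SDd² × ((Z for alpha + Z for power)/(d + delta))², with the t-based correction, and drop the ratio of group sizes;
2. say whether 3.5 is an SD or a variance, and whether it refers to a single test or to the within-subject difference. If it refers to a single test, give the correlation assumed between a subject's tests;
3. give its unit, the same as that of the margin (3.5 mL/kg/min or 1 eMET);
4. state the one-sided alpha and make it consistent with the two-tailed 0.05 analysis;
5. state the power that 19 evaluable pairs give under those inputs, in place of the present 0.9 if it differs.

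The cost is one rewritten paragraph, with no added subjects and no change in conduct. The stated power may move up or down, depending on what 3.5 proves to be.

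### The protocol states a one-sided non-inferiority hypothesis with a 1 eMET margin, but no analysis it names is linked to that margin; at their ordinary meaning its two-tailed paired tests address zero difference

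*Protocol*

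**What the plan says.** The Study Design paragraph is explicit about the type of trial: "The study design is a prospective crossover non-inferiority trial where subjects will complete 3 separate graded exercise treadmill tests". The Hypothesis section puts non-inferiority in the alternative, "limiting peak exercise when non-inferiority margin is 1 eMET". The Statistical Analysis section writes the same hypotheses in symbols, with H0: mask minus no mask ≤ -δ and H1: > -δ, and lets δ "denote the non-inferiority margin of 3.5, which is a (clinically meaningful) minimal detectable difference". The margin then enters the sample-size formula together with Z(1-α). No value of α is given there.

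The same paragraph goes on to choose the analyses. For continuous variables: "The Wilcoxon signed-rank signed test or paired-sample t-test will be used to compare continuous variables between the Mask and NoMask exercise". For repeated measures: "Mixed-effected linear regression models will be applied for the repeated measures data". McNemar's test and Pearson correlation are also listed. One rule covers all of them: "Analyses will be two-tailed and performed at significance level of 0.05". After the sample-size inputs δ does not appear again. The section names no shifted null value, no confidence limit to be set against -3.5, and no rule for declaring non-inferiority.

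**The concern.** A paired t-test or signed-rank test given without a null value, and called two-tailed, is ordinarily a test that the mean or median difference is zero. That is a different question from whether the mask costs less than 1 eMET, and the two can disagree in both directions. A small loss well inside the margin can be significantly different from zero. A loss as large as the margin can fail to reach significance when the data are noisy. A statistician who follows the section as written would report a p-value that neither supports nor refutes the trial's own alternative hypothesis. The trial's main conclusion about cloth masks depends on that comparison.

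**Working it through.** **1. The plan's own figure.** The inputs, all from the Statistical Analysis section, are δ = 3.5, σ² = 3.5, k = 1, d = 0, power 0.9, drop-out 5% and total n = 20. The formula is n per condition = (1 + 1/k)·σ²·((Z(1-α) + Z(1-β))/(d + δ))². Since α is not given, both usual values are tried:

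- σ² = 3.5, one-sided 0.05: 2 × 3.5 × ((1.645 + 1.282)/3.5)² = 4.89, so 5 per condition.
- σ² = 3.5, one-sided 0.025: 2 × 3.5 × ((1.960 + 1.282)/3.5)² = 6.00 (just above 6), so 7 per condition.
- 3.5 read as an SD (σ² = 12.25), one-sided 0.05: 17.13, so 18, or 19 with drop-out.
- 3.5 read as an SD, one-sided 0.025: 21.01, so 22, or 24 with drop-out.

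None gives 20 exactly. The nearest reading treats 3.5 as an SD, against the printed label. The documents therefore do not settle the SD of the paired difference, and a range has to be carried.

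**2. Assumptions for the check.** Evaluable pairs: 20 × 0.95 = 19, so 18 degrees of freedom. Assumed SDs of the paired difference, in mL/kg/min:

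- 1.87 = √3.5 (the printed variance, in mL/kg/min squared)
- 3.5 (3.5 read as the SD of the difference)
- 4.95 = 3.5 × √2 (3.5 as the SD within each condition, with no within-subject correlation)
- 6.55 = 3.5 × √3.5 (the printed variance, in eMET squared)

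**3. Formulas.** SE = SD/√19, and the critical value is t(0.975, 18) = 2.101. The test of zero has noncentrality (true difference)/SE. The test against the margin has noncentrality (true difference + 3.5)/SE and rejects when the lower two-sided 95% limit exceeds -3.5. Probabilities come from the noncentral t distribution.

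**4. Results.**

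| SD | SE | True loss 0.4 eMET (1.4 mL): zero test significant | True loss 1 eMET (3.5 mL): zero test non-significant | True loss 1 eMET: margin test declares non-inferiority | No true loss: margin test declares non-inferiority |
|---|---|---|---|---|---|
| 1.87 | 0.43 | 87% | about 0% | 2.5% | >99.9% |
| 3.5 | 0.80 | 38% | 1.6% | 2.5% | 98% |
| 4.95 | 1.14 | 21.5% | 17% | 2.5% | 83% |
| 6.55 | 1.50 | 14% | 40% | 2.5% | 60% |

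The two kinds of disagreement trade off. With a small SD the zero test flags losses that the protocol's own margin tolerates: at SD 1.87 and a 0.4 eMET loss, the margin test shows non-inferiority in 99.6% of trials while the zero test is significant in 87%. With a large SD the zero test often misses a loss equal to the margin. Only the margin test has an error rate that does not depend on the SD.

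**The case against.** The strongest reply is that nothing in the section forbids the right analysis. A paired t-test can be run against any null value. A mixed model for three conditions yields a cloth-minus-no-mask contrast with a confidence interval. The section opens by declaring a non-inferiority design, and a decision rule is commonly left to a statistical analysis plan, which is not at hand here. A two-sided 0.05 level is not in itself incompatible with non-inferiority, since a two-sided 95% interval serves the purpose. All of this is true. It means that a reader may not infer that the margin will certainly go untested, or that paired tests are the only analyses planned. It does not remove the point: the protocol has itself fixed the tests, sidedness and level, and none is connected to its H0/H1.

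Three further readings are tempting and not supported.

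- A reader might infer that sizing and analysis use different error rates, because the formula has Z(1-α) and the analysis is two-tailed. But α is not stated for the formula, and one-sided 0.025 would match two-sided 0.05. This is an ambiguity, not a demonstrated mismatch.
- A reader might infer that the zero test would pass an inferior mask far more often than 2.5% or 5%. That holds at SDs of 4.95 and 6.55. It fails at 1.87, the printed variance taken in mL/kg/min squared, and at 3.5.
- A reader might infer that the investigators intend to read p > 0.05 as non-inferior. The protocol nowhere says so.

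**Conclusion.** The point stands as a contradiction within the protocol and should be corrected before analysis. The stated hypothesis is one-sided and shifted by 3.5 mL/kg/min, while the stated analyses, at their ordinary meaning, test zero and are not tied to that margin. The size depends on an SD that the documents leave open. With 19 pairs, the zero test is significant for a tolerable 0.4 eMET loss in 14% to 87% of trials, and non-significant for a full 1 eMET loss in about 0% to 40%. These extremes come from opposite ends of the SD range and must not be quoted together as if they applied to one trial. The conclusion that no stated analysis answers H0/H1 does not depend on the SD.

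**What to change.** Add a primary-analysis sentence to the Statistical Analysis section: non-inferiority of the cloth mask to no mask on peak eMET is concluded if the lower limit of the two-sided 95% confidence interval for the within-subject mean difference (cloth minus no mask, from the paired analysis or a mixed-model contrast) exceeds -3.5 mL/kg/min. This is consistent with the two-tailed 0.05 level already stated. State the α used in the sample-size formula and make it match, which for this interval is one-sided 0.025. Keep tests of zero difference for secondary variables, and say that a non-significant result on them is not evidence of non-inferiority.

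The cost is a few lines of wording and no new data. Power is the caveat: with 19 pairs and no true difference, the rule has power above 99.9%, 98%, 83% or 60% at SDs of 1.87, 3.5, 4.95 and 6.55. The stated 0.9 is kept at the two smaller values and would have to be restated at the two larger ones, so the SD of the paired difference and its units should be given in the same revision.

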## Project Timeline

All testing expected to be completed within 2 weeks, followed by data and statistically analysis. We intend to have this study written up and published prior to the opening of public gyms in Ohio.

## Budget

Funding by [name] and Pulmonary Institute

## Appendix

ACSM's 2015 preparticipation health screening guidelines

[figure not shown]

## Step 1

### SYMPTOMS

#### Does your client experience:

- ☐ chest discomfort with exertion
- ☐ unreasonable breathlessness
- ☐ dizziness, fainting, blackouts
- ☐ ankle swelling
- ☐ unpleasant awareness of a forceful, rapid or irregular heart rate
- ☐ burning or cramping sensations in your lower legs when walking short distance

If you **did** mark any of these statements under the symptoms, **STOP**, your client should seek medical clearance before engaging in or resuming exercise. Your client may need to use a facility with a **medically qualified staff**.

If you **did not** mark any symptoms, continue to steps 2 and 3.

## Step 2

### CURRENT ACTIVITY

Has your client performed planned, structured physical activity for at least 30 min at moderate intensity on at least 3 days per week for at least the last 3 months?

Yes ☐ No ☐

|                                |                                                                                                                                                                                                                                                                                                                                                                                                               |
|--------------------------------|---------------------------------------------------------------------------------------------------------------------------------------------------------------------------------------------------------------------------------------------------------------------------------------------------------------------------------------------------------------------------------------------------------------|
| §Exercise Participation        | Performing planned, structured physical activity at least 30 min at moderate intensity on at least 3 d · wk  for at least the last 3 mo                                                                                                                                                                                                                                                          |
| *Light Intensity Exercise      | 30%–39% HRR or $\dot{V}O_2R$ , 2–2.9 METs, RPE 9–11, an intensity that causes slight increases in HR and breathing                                                                                                                                                                                                                                                                                            |
| **Moderate Intensity Exercise  | 40%–59% HRR or $\dot{V}O_2R$ , 3–5.9 METs, RPE 12–13, an intensity that causes noticeable increases in HR and breathing                                                                                                                                                                                                                                                                                       |
| ***Vigorous Intensity Exercise | ≥60% HRR or $\dot{V}O_2R$ , ≥6 METs, RPE ≥14, an intensity that causes substantial increases in HR and breathing                                                                                                                                                                                                                                                                                              |
| ‡Cardiovascular (CV) Disease   | Cardiac, peripheral vascular, or cerebrovascular disease                                                                                                                                                                                                                                                                                                                                                      |
| ‡‡Metabolic Disease            | Type 1 and 2 diabetes mellitus                                                                                                                                                                                                                                                                                                                                                                                |
| ‡‡‡Signs and Symptoms          | At rest or during activity. Includes pain, discomfort in the chest, neck, jaw, arms, or other areas that may result from ischemia; shortness of breath at rest or with mild exertion; dizziness or syncope; orthopnea or paroxysmal nocturnal dyspnea; ankle edema; palpitations or tachycardia; intermittent claudication; known heart murmur; unusual fatigue or shortness of breath with usual activities. |
| ‡‡‡‡Medical Clearance          | Approval from a health care professional to engage in exercise                                                                                                                                                                                                                                                                                                                                                |
| ¶ACSM Guidelines               | See ACSM's Guidelines for Exercise Testing and Prescription , 10th edition, 2018                                                                                                                                                                                                                                                                                                                       |

|                    | Not at all                        | Mildly | Strongly |
|--------------------|-----------------------------------|--------|----------|
| Humid              |                                   |        |          |
| Hot                |                                   |        |          |
| Breathe resistance |                                   |        |          |
| Itchy              |                                   |        |          |
| Tight              |                                   |        |          |
| Salty              |                                   |        |          |
| Unfit              |                                   |        |          |
| Odour              |                                   |        |          |
| Fatigue            | 
0 1 2 3 4 5 6 7 8 9 10 |        |          |

|                    | Comfortable                       | Uncomfortable | Extremely Uncomfortable |
|--------------------|-----------------------------------|---------------|-------------------------|
| Overall Discomfort | 
0 1 2 3 4 5 6 7 8 9 10 |               |                         |
